### Provisions for post-trial care {30}

Participants allocated to group 1 (CR + sham tDCS) can receive additional 32 training sessions with CR + active tDCS after the end of the complete trial.

### Outcomes {12}

#### Primary outcome measures

The feasibility of the interventions will be evaluated by procedural statistics (retention and participation rates), and the acceptability will be assessed by means of an interview with the participants. Additionally, preliminary data will be obtained for daily and cognitive functioning, and changes between assessments will be evaluated (first baseline (*T*_0_) to the second baseline (*T*_1_); second baseline (*T*_1_) to post-intervention (*T*_2_); second baseline (*T*_1_) to the 6-month follow-up (*T*_3_); and post-intervention (*T*_2_) to follow-up (*T*_3_)). Assessments will include (a) *daily functioning* measured by the Life Skills Profile (LSP [45];); (b) *cognitive functioning* measured by a set of cognitive tests selected to represent all MATRICS domains [46]: Controlled Oral Word Association Test (COWAT [47];), Modified Card Sorting Test (MCST, [48]), Digit span forward and backward [49], Rey Complex Figure Test and Recognition Trial (RCFT [50];), 15-Word Learning Task (WT-15, [51]), and Stroop Color and Word Test [52]; (c) *subjective cognitive functioning* measured by the Cognitive Failures Questionnaire (CFQ [53];) and (d) *observed cognitive functioning* measured by the Nurses’ Observation Scale of Cognitive Abilities (NOSCA [54];).

#### Secondary outcomes

##### Superior effect of active tDCS

The difference between CR + active tDCS and CR + sham tDCS in the change of daily and cognitive functioning will be assessed by the same measures described above.

##### Acceptability of tDCS

The acceptability of tDCS will be evaluated by means of an interview with the participant post-intervention.

##### Self-reported negative symptoms

Changes in self-reported negative symptoms between assessments will be measured by the Self-Evaluation of Negative Symptoms (SNS [55];).

### Participant timeline {13}

See Table 1.

**Table 1 Tab1:**
[figure not shown]
Schedule of enrolment, interventions, and assessments

*CR* cognitive remediation, *COWAT* Controlled Oral Word Association Test, *LSP* life skills profile, *MCST* Modified Card Sorting Test, *NOSCA* Nurses’ Observational Scale of Cognitive Abilities, *PANSS* The Positive and Negative Syndrome Scale, *RCFT* Rey Complex Figure Test, *SNS* Self-evaluation of Negative Symptoms, *tDCS* Transcranial direct current stimulation, *WAIS-IV* Wechsler adult intelligence scale IV, *WT-15* 15-word learning task

### Sample size {14}

For this pilot trial, the sample size is based on Whitehead et al. [56], who evaluated and compared methods for sample size calculation for pilot studies in order to minimize the recruitment of participants across pilot and main trial while maintaining the average power. The authors advise a pilot sample size of 10 participants per treatment arm if the estimated standardized effect size of the main trial is medium or large. We estimated a medium effect size based on the results of a large meta-analysis that demonstrated moderate effects of CR on cognition (effect size 0.45) and daily functioning (effect size 0.42) [18]. Taking into account a drop-out percentage of 20%, a total of 26 participants are required in order to reach a sample size of 10 participants who complete the trial per treatment arm. By considering the pilot study as a part of the main trial, this method allows to include the pilot data, if the trial is extended to a large randomized trial with a similar design.

### Recruitment {15}

The investigators will organize information meetings in the residential treatment and sheltered housing facilities to recruit participants. Additionally, nurses, psychologists, and psychiatrists will be informed about the study aims and design in information meetings and through personal communication, and they will be asked to look out for eligible participants. They will ask service users whether they give consent to be approached by the investigators of the current research project. Service users who show interest in participating will be asked to contact one of the researchers or, when desired, one of the researchers will contact them. Contact information will be given in the participant information letter. The information letter will cover all relevant information the person needs to decide whether or not to participate in the study. Service users who agree will then be informed in detail by the researchers about the goals and procedures of the experiment, both by way of an information letter and during an individual appointment. Each participant will receive a financial reimbursement of €10 per hour for the first two and the last measurement, and €15 for the third measurement (total €45).

### Assignment of interventions: allocation

#### Sequence generation {16a}

Participants will be randomly assigned to CR + sham tDCS (group 1) or CR + active tDCS (group 2) with a 1:1 allocation as per a computer-generated randomization plan using permuted blocks of random sizes. The block sizes will not be disclosed to ensure concealment.

#### Concealment mechanism {16b}

A randomization sequence will be generated by a randomization plan generator (http://randomization.com). The tDCS device is pre-programmed with codes that are linked to either real or sham stimulation. Twenty-six codes, which are printed in the manual, will be selected randomly (13 for sham stimulation, 13 for real stimulation) and linked to the randomization sequence. The manual page with the codes and the randomization sequence will be kept in two separate sealed envelopes which will remain closed until the completion of the data collection.

Only the sequence of the codes will be accessible during the trial, which cannot be linked to real or sham stimulation without the randomization sequence or the manual page. When participants complete the second baseline measurement (*T*_1_), the first available code in the sequence will be coupled to the participant number.

#### Implementation {16c}

An independent researcher will generate the allocation sequence, select the tDCS codes, link them to the randomization sequence and seal the envelopes. The investigators will enroll participants, link the tDCS code to the participant number following the second baseline measurement (*T*_1_), and communicate the code to the CIRCuiTS therapist. The randomization sequence and the block sizes will not be disclosed until all participants completed the follow-up measurement (*T*_3_). Thus, randomization will be conducted without any influence of the investigators, raters, or therapists.

### Assignment of interventions: blinding

#### Who will be blinded {17a}

Using the allocation procedure described above the trial will be triple-blind to the tDCS experimental condition; the investigators, the CIRCuiTS therapist, and the participant will stay blind to the tDCS treatment condition. The CIRCuiTS therapist and participant will be asked to indicate whether the participant received either active or sham stimulation in session 10 of the intervention and at *T*_2_. The participants will be informed about the type of treatment they have received after completion of the trial. As all participants will receive CIRCuiTS, the investigators, CIRCuiTS therapist, and participants will not be blind to the CIRCuiTS experimental condition.

Research assistants (at least BA level psychologists) will be trained to administer the assessments. They will be blind to the experimental condition (both tDCS and CIRCuiTS) of the participants, as they will not receive any information regarding the aims and design of the trial, nor of the intervention. Guessing the aim of the study and the allocation group of the participant (“Experimental,” “Control,” “There is no control or experimental condition,” or “I don’t know”) after every assessment will be used to evaluate whether blinding was successful.

#### Procedure for unblinding if needed {17b}

Not applicable, as there are no circumstances during the trial under which unblinding will be permissible.

### Data collection and management

#### Plans for assessment and collection of outcomes {18a}

##### Testing procedure

Outcome measures for both groups will be assessed before (*T*_0_) and after the waiting period (*T*_1_), after completion of the treatment (*T*_2_), and 6 months post-treatment (*T*_3_). After T_2_, an interview will be conducted. All tests and measures are described below. The assessments will be administered by trained research assistants. Demographical information will be obtained from the patient file. In order to describe the clinical characteristics of the participant group at baseline, the Positive and Negative Syndrome Scale (PANSS [57];) is used. The PANSS is part of the yearly Routine Outcome Monitoring screening, which is performed by a trained nurse. Though psychiatric symptoms in service users of residential and sheltered living departments are generally stable (and for which the yearly screening data will suffice), it is possible that symptoms in some service users have fluctuated in the period between the last PANSS interview and the start of the study. To address possible fluctuations in symptoms, the treating clinician will be consulted preceding the start of the first baseline assessment. In case of changed symptomatology, an additional PANSS will be administered by a trained nurse, which will take 30 min.

#### Baseline measures

##### Demographical information

The following demographical and clinical information will be collected: year of birth, gender, nationality, level of education, level of education of parents, main diagnosis, comorbid diagnoses, age at first hospitalization, medication use, psychiatric disorders of parents and siblings, relevant medical events, neurological disorders, and alcohol and drug use.

##### Severity of clinical symptoms

The Positive and Negative Syndrome Scale (PANSS, [57]) is a semi-directive interview developed, standardized, and validated for the typological and dimensional characterization of schizophrenia. It consists of 30 items; each scored on a 7-point scale and divided between a scale for positive symptoms, a scale for negative symptoms, and a general psychopathology scale. The total PANSS scale is judged as stable, valid, and reliable [57]. The Dutch version of the PANSS is validated by Wolthaus et al. [58].

##### Expectations

As participants’ expectations may influence the cognitive performance following tDCS administration [59], participants’ expectations will be assessed prior to the start of the intervention. They will be asked if they believe (1) that the intervention can improve cognitive and daily functioning in general, and (2) that the intervention can improve their own cognitive and daily functioning.

#### Outcome measures

##### Feasibility

The feasibility will be determined by the retention and participation rates of the intervention.
Retention: The intervention will be considered feasible if > 60% of the sample completes the study. The threshold for indicative feasibility was determined based on the retention and participation rates in previous studies. Previous CR studies in inpatient populations with schizophrenia had retention rates of 58–92% [20, 27, 60, 61]. Previous studies that combined cognitive training and non-invasive brain stimulation in people with schizophrenia had retention rates of 58–100% [62, 63].Participation rates: The intervention will be considered feasible if participants complete > 62.5% (i.e., 20 sessions) of the intervention sessions, as in the RCT of CIRCuiTS by Reeder and colleagues, the developers of CIRCuiTS judged that a minimum therapy course comprises 20 sessions [27].

##### Acceptability

The Theoretical Framework of Acceptability developed by Sekhon et al. [64] will be used to evaluate the acceptability of the intervention. Within this theoretical framework, acceptability is defined as “a multi-faceted construct that reflects the extent to which people delivering or receiving a healthcare intervention consider it to be appropriate, based on anticipated or experienced cognitive and emotional responses to the intervention” and consists of seven component constructs: Affective attitude, burden, intervention coherence, ethicality, opportunity costs, perceived effectiveness, and self-efficacy. To evaluate acceptability within the seven components of acceptability, all participants will be interviewed regarding these components following the post-intervention assessment (*T*_2_). This interview will take approximately 15 min.

##### Functional outcome measure

The Life Skills Profile (LSP [45];) is a questionnaire consisting of 39 questions that are scored on a 4-point scale (lower score indicates higher life skills). The questionnaire is developed from a positive mental health philosophy, by emphasizing “life skills” rather than “lack of life skills” and measures a range of aspects related to successful community or hospital living: (1) self-care, (2) non-turbulence, (3) social skills, (4) communication, and (5) responsibility. The LSP has shown good psychometric properties when completed by residential staff and case managers [45] and will be completed by a participants’ case manager.

##### Cognitive outcome measures

The tests of the cognitive test battery were chosen to represent the domains of the Measurement and Treatment Research to Improve Cognition in Schizophrenia (Nuechterlein et al., 2008) test battery. The administration of the MATRICS battery is not feasible in the target group due to its length. Hence, we chose tests that match the skills of the target group.
*Speed of processing*. Controlled Oral Word Association Test (COWAT [47];) is a test for verbal fluency and speed of processing. Participants have to name as many words as possible within a time span of 60 s, beginning with a given letter. The score is the total number of words of three trials. This test will take 10 min.*Attention and working memory.* Digit Span forward (WAIS-IV, [49]) is a test for immediate auditory attention. The test leader reads sequences of digits out loud, gradually increasing the digit span. The participants are asked to repeat the digits in the same order. The score is determined as the number of correctly recalled sequences. Digit Span backward (WAIS-IV [49];) is a test for working memory. It is executed similarly as the previous test; however, the digits have to be repeated in reverse order. Both tests will take 5 min.*Visual memory.* The Rey Complex Figure Test (RCFT) is a measure for visual memory [50]. The test leader presents a complex figure that participants are asked to copy (copy trial). Thirty minutes later, the participants are asked to draw the complex figure from memory (recall trial). This test will take approximately 5 min.*Verbal memory.* The 15-word learning task, immediate memory (WT-15 [51];) is a test for verbal memory. The test leader reads 15 words out loud and participants are asked to recall as many words as possible. This procedure is repeated five times. The score is determined as the total number of reproduced words (max. 75). Additionally, after continuing with the test battery for 15 min, the participant will be asked to name as many words as they can remember (free recall). This test will take approximately 20 min to complete.*Reasoning and problem solving.* The Stroop Color and Word Test [52] is used to test speed of processing, inhibition, cognitive flexibility, and cognitive control. The participants first perform a basic task, which is reading the names of colors. The performance on this task is compared with the performance on a task in which the ink color of incongruent color words has to be named. Hence, a habitual response needs to be suppressed in support of an unusual one. The increase in time taken to perform the latter task compared with the basic task is referred to as “the Stroop interference effect” and provides a general measure of executive functioning. The total duration of the Stroop Task will be approximately 5 min.*Reasoning and problem solving.* Modified Card Sorting Test (MCST [48];) is a test for cognitive flexibility and reasoning. The test leader presents four stimulus cards with different shapes and colors. Participants receive a pile of 48 cards and are asked to lay down the cards one by one on the four presented cards, following a rule that the participant has to discover. The score is determined as the number of correct categories and the number of errors (e.g., perseverations). The MSCT is a simplified version of the Wisconsin Card Sorting Test and is easier to understand for people with a disorder and will take approximately 10 min.*Subjective cognitive functioning.* The Cognitive Failure Questionnaire (CFQ) is a questionnaire to measure subjective cognitive functioning [53, 65]. The scale includes 25 questions that represent the cognitive subdomains of attention and memory. The questionnaire can be completed by the participants and takes approximately 5 min.*Observed cognitive functioning.* The Nurses’ Observation Scale of Cognitive Abilities (NOSCA [54];) is a behavioral rating scale to examine cognitive abilities. The scale includes 39 items that are scored on a 4-point scale, and it comprises eight subscales: attention, perception, memory, orientation, thoughts, language, and praxis. The NOSCA will be completed by the participants’ case manager. This scale will take approximately 10 min to complete.

##### Clinical outcome measure

Participant’s negative symptoms at baseline will be assessed with the Self-Evaluation of Negative Symptoms (SNS [55];). This self-report questionnaire contains 20 items covering the five domains of negative symptoms (social withdrawal, diminished emotional range, avolition, anhedonia, and alogia) and can be scored on a three-point Likert scale, based on the feelings during the previous week. The administration of the SNS will take approximately 5 min. The questionnaire is designed and validated by Dollfus et al. [55] and has shown good psychometric properties and is well-tolerated by service users. The English version of the questionnaire is translated into Dutch by the investigators of this study, back-translated to French by a native French speaker, and approved by [name]. [name].

### Plans to promote participant retention and complete follow-up {18b}

As the intervention has a duration of 4 months and takes place twice weekly, it is possible that participants will miss sessions, for example, because of illness, vacation, or important (medical) appointments. In the RCT of CIRCuiTS by Reeder and colleagues, the developers stated that a minimum therapy course comprises 20 sessions, which includes both sessions with the therapist and independent homework sessions [27]. Accordingly, participants will be considered completers, if they complete at least 20 sessions, and non-completers, if they complete less than 20 sessions. As we are interested in the feasibility and acceptability of the intervention, participants who discontinue the intervention protocol will be encouraged to take part in the intervention evaluation interview at the moment of discontinuation. Participants who drop out or deviate from the intervention protocol (i.e., complete less than 20 sessions) will be invited back for the assessments at *T*_2_ and *T*_3_.

### Data management {19}

In the trial, all data will be entered digitally at Lentis Psychiatric Institute. Original study forms will be saved in files and stored at the study site. Participant files are to be stored in numerical order and stored in a secure place for a period of 15 years. The data entry screens will resemble the paper forms. Data integrity will be enforced through range checks and consistency checks. Modifications to data written to the database will be documented in a separate file. A complete backup of the database will be performed once a month. A data management plan will be developed to summarize all procedures of data management.

### Confidentiality {27}

All data received from participants will be processed in a strictly confidential manner. Except for the written consent and the proof of payment, no other questionnaires or documents will contain any personal data (name, address, date of birth) of the participants, but will be attributed by a code. The participant code can only be traced back by accessing a protected key file. The password to the key file will only be shared with the researchers who are involved in the data collection. Researchers, other than those immediately involved in the data collection and in the intervention, only have access to fully anonymous files, which cannot be traced back to a specific individual. Data used for publication are also completely anonymous. All handling of personal data will comply with the Dutch General Data Protection Regulation (Dutch: Algemene Verordening Gegevensbescherming (AVG)).

### Plans for collection, laboratory evaluation, and storage of biological specimens for genetic or molecular analysis in this trial/future use {33}

Not applicable, no samples collected.

### Statistical methods

#### Statistical methods for primary and secondary outcomes {20a}

##### Acceptability

The acquired data from the Intervention Evaluation Interview will be analyzed qualitatively using the qualitative data analysis and research software ATLAS-ti.

##### Cognitive and functional outcome measures

For all the tests, sum scores will be calculated and related to normative data for each individual. Averages and standard deviations will be calculated per training condition. Subsequently, all variables will be checked for normality. To measure demographical and baseline differences between the two groups, an independent sample *t*-test will be performed.

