##### CR vs. treatment as usual

The mean differences in outcomes of both groups combined will be compared to the waitlist period using multilevel modeling to assess the effect of CR over treatment as usual. A two-level model will be built with subject (level 2) and time point of assessment (level 1) entered as levels. The significance of the fixed regression effects is tested using the appropriate *t-*test (*α* = .05).

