##### CR + active tDCS vs. CR + sham tDCS

The mean differences in outcomes between groups 1 and 2 will be compared using multilevel modeling to assess whether active tDCS in combination with CR is superior in improving cognitive functioning and daily functioning over CR + sham tDCS. A two-level model will be built with subject (level 1) and time point of assessment (level 2).

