However, the use of a multiple baseline design has some disadvantages and challenges. Firstly, the assessments happen over a period of time and the control condition will, on average, contribute data from an earlier calendar time. Therefore, time effects could influence the results. However, psychiatric symptoms and cognitive impairments are generally stable in the targeted inpatient population, which minimizes the risk of time effects. A second challenge arising due to the presence of a waiting period is that participants might become less engaged during the waiting period and drop out before the intervention has started. Thus, it will be important to keep regular contact with the participants during the waiting period. The therapist will contact all participants once a month, to keep the engagement process as similar as possible across the whole group. While keeping the participants engaged may be a challenge, the contact moments allow building up a therapeutic relationship with the participant which could relate to higher motivation during the intervention. Thirdly, as all participants receive CR, the investigators, the therapist, and the participants are not blind to whether or not participants receive CR. To control for possible influences of this disadvantage to the assessments, assessors will be kept blind to the intervention conditions by not disclosing the study aims and design to them.

Another challenge in this trial is the evaluation of the superiority of adding active tDCS to the cognitive remediation over sham tDCS. Active tDCS will be added to the treatment of only half of the participants, and the efficacy will be analyzed in a group analysis. The chosen study design requires fewer participants than a traditional randomized controlled trial to investigate the CR efficacy given the within-subject comparison. Yet, because of the small sample size and the expectation that CR on its own can improve cognitive and daily functioning, the power to detect significant differences between the groups with respect to tDCS efficacy is low. While statistical significance may be difficult to achieve, this pilot study can at a minimum identify a trend towards superior treatment effects of combined CR and tDCS as compared to CR only. If the addition of tDCS seems to have an additive effect on CR, we aim to initiate a multicenter randomized controlled trial to further investigate the efficacy.

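### The active-versus-sham model does not say how the two pre-randomisation scores are used; if it tests change from T1 it loses precision, and the planned baseline t-tests do not help

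*Protocol article*

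**What the plan says.** - **Timing of allocation.** Under Implementation {16c} the investigators "link the tDCS code to the participant number following the second baseline measurement", that is, after T1. Every outcome measured at T0 and T1 therefore precedes randomisation.
- **Outcome for tDCS.** Superior effect of active tDCS defines it as "The difference between CR + active tDCS and CR + sham tDCS in the change of daily and cognitive functioning". Primary outcome measures lists the changes of interest: T0 to T1, T1 to T2, T1 to T3 and T2 to T3. Both changes that run from before to after treatment start at T1.
- **Model.** CR + active tDCS vs. CR + sham tDCS states: "The mean differences in outcomes between groups 1 and 2 will be compared using multilevel modeling". It gives two levels, subject and time point. It does not say which time points enter, which term is tested, or whether arm means at T0 and T1 are free or held equal. No baseline covariate is mentioned.
- **Baseline.** Cognitive and functional outcome measures states: "To measure demographical and baseline differences between the two groups, an independent sample" and names the t-test as the method.
- **Power.** The Discussion concedes that "the power to detect significant differences between the groups with respect to tDCS efficacy is low".

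**The concern.** Randomisation after T1 makes the arms equal in expectation at both T0 and T1. An analysis that uses this gains precision at almost no cost. One that takes each participant's change from T1 gives it up: change from a single noisy baseline has larger variance than a baseline-adjusted comparison, and it carries chance imbalance at T1 into the estimate. A model with a free arm effect at every visit behaves the same way, because it lets the arms differ before randomisation.

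The baseline t-tests do not fill the gap. Under randomisation the null hypothesis is true by design. A non-significant result at this size reassures nobody, and no action is attached to a significant one. The items listed under Demographical information include gender, nationality and main diagnosis, for which a t-test of means is not meaningful.

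The stake is the tDCS signal. The Discussion hopes to see at least a trend and ties a multicentre trial to it, and the Sample size section allows pilot data to be carried into an extended trial of similar design.

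**Working it through.** **Inputs from the protocol.** 10 completers per arm, 20% drop-out, 26 in total (Sample size {14}); 1:1 allocation (Trial design {8}); visits T0, T1, T2, T3, with T0, T1 and T2 separated by 16-week periods; effect size 0.45 for CR on cognition (Sample size), used below for scale only because it is not a tDCS effect.

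**Assumptions.** The protocol gives no within-person correlation r, so it is varied. The outcome SD is set to 1 at each visit. The contrast worked is T2.

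**1. The plan's own figure.** 10/(1 − 0.20) = 12.5, rounded up to 13 per arm, 26 in total. It reproduces.

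**2. What a baseline t-test can show.** With 13 per arm the SE of a baseline difference is √(2/13) = 0.39 SD. An observed imbalance of 0.5 SD gives 0.5/0.39 = 1.3, not significant, although it would matter to the estimate.

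**3. Variance under equal correlation at all visits.**
- Change from T1 (also what a saturated arm-by-time random-intercept model gives): 2(1 − r)
- One common pre-treatment arm difference over T0 and T1: 1.5(1 − r)
- T0 and T1 as covariates, or arm means held equal at T0 and T1: (1 − r)(1 + 2r)/(1 + r)

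| r | change from T1 | common pre-treatment difference | adjusted or constrained | cut vs change from T1 |
|---|---|---|---|---|
| 0.5 | 1.000 | 0.750 | 0.667 | 33% |
| 0.7 | 0.600 | 0.450 | 0.424 | 29% |
| 0.8 | 0.400 | 0.300 | 0.289 | 28% |
| 0.9 | 0.200 | 0.150 | 0.147 | 26% |

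At r = 0.7 the middle model loses only 1 − 0.424/0.450 = 6%. A model that already holds baseline means equal loses nothing.

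**4. Variance if correlation decays with time (first-order autoregressive, r between adjacent visits).** T0 then adds nothing beyond T1, and the adjusted variance is 1 − r². The ratio to change from T1 is (1 − r²)/[2(1 − r)] = (1 + r)/2, so the cut is 25%, 15% and 10% at r = 0.5, 0.7 and 0.8.

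**5. Cost of estimating covariates.** With q covariates and N participants the variance is inflated on average by 1 + q/(N − q − 3).
- Equal correlation, r = 0.7, one covariate (the mean of T0 and T1): N = 20 gives 0.424 × 1.0625 = 0.450, a net cut of 25%; N = 26 gives 26%.
- Same, two covariates: N = 20 gives 0.424 × 1.133 = 0.480, a net cut of 20%.
- Decay, r = 0.7, T1 alone: N = 20 gives 0.510 × 1.0625 = 0.542, a net cut of 10%. With T0 and T1 separately, 0.510 × 1.133 = 0.578, a net cut of 4%.

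**6. On the scale of the trial (equal correlation, r = 0.7, before the cost in step 5).** SE = √(2 × variance/n). At 13 per arm it falls from 0.30 to 0.26 SD; at 10 completers per arm, from 0.35 to 0.29 SD. Approximate two-sided power at 10 per arm and an effect of 0.45 is Φ(0.45/0.346 − 1.96) = 25% against Φ(0.45/0.291 − 1.96) = 34%.

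**7. Chance imbalance.** A one-SE imbalance at T1 (0.39 SD at 13 per arm) shifts a change-from-T1 estimate by (1 − r) × 0.39 = 0.12 SD at r = 0.7, about a quarter of 0.45.

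**The case against.** A reader might infer that the plan uses change scores and baseline t-tests in place of adjustment, and so throws away about 30% of its precision. The protocol does not support that reading, for three reasons.

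- **A difference in change is an estimand, not an estimator.** The methods section specifies a multilevel model and computes no change score. A constrained longitudinal model also estimates a difference in change. Since the parameterisation is not given, the loss could be nil, about 6%, or 26% to 33%.
- **The t-tests are said only to measure differences.** Nothing makes them a substitute for adjustment or lets them alter the treatment model.
- **The 30% figure needs two assumptions that the protocol does not make:** that change from T1 is the tested contrast, and that correlation is equal across visits. With decaying correlation the figure is smaller, and at 20 completers the cost of covariates takes a visible part of it.

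It can also be said that covariates and model terms belong in an analysis plan, and that this is a secondary question in a pilot whose feasibility criteria are untouched. Both are fair and limit the weight of the point. They do not remove it. The t-tests are a stated choice, not an omission. The listed pre-to-post changes do start at T1 alone. And the model sentence needs rewriting anyway: it numbers subject as level 1 and time point as level 2, the reverse of the CR comparison ("A two-level model will be built with subject (level 2) and time point of assessment (level 1) entered as levels"), although visits are nested within subjects.

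**Conclusion.** The point holds in conditional form. The baseline t-tests are uninformative between randomised arms and unsuitable for the categorical items; that rests on the text alone. The active-versus-sham comparison is framed as change, with pre-to-post changes starting at T1 and no stated use of T0 and T1 as pre-randomisation information. If change from T1 is what is tested, adjustment would cut variance by 26% to 33% (equal correlations of 0.9 to 0.5) or about 10% to 25% (decaying correlation, 0.8 to 0.5), before the cost of one or two degrees of freedom. If arm means are already constrained equal at baseline, there is no loss. All correlations are assumed. The gain does not rescue the comparison: in the illustration power moves from about 25% to 34%, low either way, as the Discussion already accepts.

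**What to change.** 1. Replace the baseline t-tests with descriptive summaries by arm: means and SDs for scores, counts and percentages for categorical items.
2. In the active-versus-sham section, state one of two models:
   - T2 and T3 as outcomes, with each participant's T0 and T1 scores as covariates; or
   - all four visits as outcomes, with arm means constrained equal at T0 and T1 and arm effects only at T2 and T3.
3. If degrees of freedom are a worry, the mean of T0 and T1 can serve as a single covariate. This is efficient when both scores correlate about equally with later ones. If correlation is expected to fall with time, T1 should keep its own weight, and in the constrained model the covariance should be allowed to reflect the decay.
4. Correct the level numbering in the same sentence.

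The cost is wording and up to two degrees of freedom. No new data are needed. The choice should be recorded before the allocation codes are opened.
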